#### 2.3.3. Professionals Experts

(a) Physicians: Physicians specializing in health education and promotion are responsible for devising the experimental protocol and conducting meetings with stakeholders (policy makers, schools and high school directors). The physicians will create the study design, and perform and revise the evaluation process of the present study. 

(b) Nutritionists: Nutritionists specializing in health education and promotion are responsible for the recruitment of ACs from high schools and younger school peers from primary schools via meeting with professors and directors. Nutritionists will support the study design and perform evaluations of the primary and secondary outcomes of the present study. Furthermore, nutritionists are responsible for the standardized direction of AC activities and their implementation in primary schools. 

(c) Managers: Managers will coordinate the professionals participating in the study, supervise the scientific work and evaluate the cost of the study activities.

### 2.4. Intervention 

#### 2.4.1. Selection of Adolescents and Process of Contact in High Schools

First, teachers from high schools will choose the ACs while following the inclusion criteria. When ACs are chosen, professionals will coordinate the visits in high schools to implement the training of ACs. The directors of high schools will plan an appropriate schedule for conducting the training of ACs (respecting the total hours of training), and professionals will go to the high schools to train the ACs at the agreed upon hours. The training will be implemented during different subject hours (natural science, tutorial, physical education and sports) or extracurricular hours so that lessons from the same subject are not affected. Then, the ACs of each high school will design one activity (1 for the secondary aim), and they will present the activity to their AC peers of other high schools in a combined session at Universitat Rovira i Virgili, considering that all the ACs will have to implement the 4 activities in primary schools. After this combined session, professionals of Universitat Rovira i Virgili will standardize each activity in each of the high schools 15 days before the implementation of the activity in the primary schools. Finally, the ACs will implement the activity in the primary schools. Then, to avoid long journeys of the ACs from high school to primary school and the loss of academic hours, primary schools located within 10 min around the high school will be chosen. 

Additionally, professionals of Universitat Rovira i Virgili will have meetings with directors of primary schools to plan 2 h of activity implementation over the first academic course (1 h in April and 1 h in May 2016) and then 2 h over the second academic course (1 h in October and 1 h in November 2016). Children in primary schools will receive only 2 activities (1 h/activity) over the first academic course (2015–2016) and 2 activities (1 h/activity) over the second academic course (2016–2017), in curricular hours.

#### 2.4.2. Training of Adolescents in High Schools and Implementation of Activities in Primary Schools

For the high school interventions, the ACs will receive an initial 16-h training session in each high school (24–32 ACs per high school), as described in Table 1, which includes the following. 

Education on healthy lifestyles, social marketing and health communication theory (2 h): 

(a) Health promotion: (a.1) Nutrition topics: basic concepts of nutrition, such as food groups and recommendations for adolescents; and (a.2) healthy lifestyles: recommendations for maintaining healthy lifestyles, such as increasing physical activity, decreasing sedentary habits, increasing fruit and vegetable consumption and eating a healthy breakfast.

(b) Social marketing: (b.1) Social marketing concepts and (b.2) the following 8 SMBC applied to the present project: Customer orientation: To gear the intervention towards younger school peers in primary schools.Behavior: To change behaviors by encouraging healthy lifestyles using knowledge-based theories.Theory: To use behavioral theories on behavioral change: involvement of adolescents in projects focused on youth populations.Insight: To motivate adolescents and younger school peers: adolescents are closer in age to their younger school peers and therefore understand the interests of this younger population.Exchange: To evaluate the costs of healthy lifestyle changes.Competition: To identify the difficulties faced by younger school peers in following a healthy lifestyle, and to involve stakeholders in the intervention: high schools, primary schools, parents, the local community and local food markets.Segmentation: To select a specific population: adolescents in the first and second years of high school and younger school peers in the third and fourth grades of primary schools in Reus.Methods mix: To use different methods to transmit the healthy lifestyle messages (activities implemented in the school, visual material, and products tasting).

(c) Communication of healthy messages: tools to transmit healthy messages to younger school peers using peer-led methodology. 

-The ACs will design 4 activities based on the 8 SMBC and will be supervised by the physicians and nutritionists specializing in health education and promotion (6 h). The 26 ACs for each of the 4 intervention high schools will lead 4 activities involving healthy lifestyles, with a total of 104 ACs.-Exhibition of activities designed by the ACs for the ACs of the other high schools (2 h).-Standardization and training in each high school regarding the 4 activities designed by the ACs (6 h). The AC activities will be standardized with those of other high school ACs to accurately implement each activity in all of the primary school interventions. To achieve standardization, the activities will be written as theatre scripts, and the ACs will repeat the activities until all of the ACs transmit the same health message.-In groups of 2–6 ACs from the same high schools, the ACs will implement the activities designed for primary schools (4 h) according to Table 1.

In general, the ACs from four intervention high schools will implement the 4 activities for their younger school peers in 8 nearby primary schools as described in Figure 2.

### 2.5. Primary and Secondary Outcomes

The expected primary outcomes are to increase the percentage of younger school peers who consume ≥1 fruit/day and practice ≥4 h/week of physical activity. The secondary outcomes are to increase the percentage of younger school peers who consume ≥1 vegetable/day and to decrease the percentage of younger school peers who have sedentary behaviors, consume a large number of sugary drinks/day and visit fast food restaurants more than once/week. 

To evaluate the primary and secondary outcomes, younger school peers from the intervention and control groups will answer a questionnaire before and after the control and intervention group interventions composed of 4 validated questionnaires:

(a) Fruit and vegetable consumption and fast food restaurant frequency: the EnKid questionnaire [21].

(b) Physical activity practice: the AVall questionnaire [22].

(c) Sedentary behavior (time spent watching TV or/and playing videogames and using the computer): the Health Behavior in School-aged Children (HBSC) questionnaire [23].

(d) Sugary drink consumption: the HABITS questionnaire [24].

### 2.6. Sample Size

The sample size of this EYTO-kids project is calculated to detect a 5% rate difference among younger school peers who consume ≥1 fruit/day or practice ≥4 h/week of physical activity between the intervention and control groups. For an alpha risk of 0.05 and a beta risk of 0.1 in a bilateral comparison, 301 primary schoolchildren are required in the first group (intervention), and 301 are required in the second group (control). An estimated 30% rate loss takes into account the losses observed in the previously conducted EYTO study [19].

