## Abstract

Introduction: The EYTO-kids (European Youth Tackling Obesity in Adolescents and Children) study aims to increase fruit and/or vegetable consumption and physical activity, decrease sedentary lifestyles, and reduce the intake of sugary drinks and fast food using an innovative methodology based on social marketing and youth involvement. Methods: This study is a pilot school-based cluster randomized controlled 10-month intervention spanning two academic years (2015–2016 and 2016–2017), with eight primary schools and three high schools randomized into and designated the control group and eight primary schools and four high schools designated the intervention group in Reus, Spain. At least 301 younger school peers per group should be included. At the intervention high schools, the adolescent creators (ACs) receive an initial 16-h training session. In total, 26–32 high school ACs (12–14 years) from the four high schools will design and implement four health-promotion activities (1 h/each) for their younger (8–10 years), primary school peers. The control group will not receive any intervention. The outcomes (fruit, vegetable, fast food and sugary drink consumption; physical activity; and sedentary behaviors) of the control and intervention groups will be measured pre- and post-intervention. Conclusion: This study describes a protocol for pilot, peer-led, social marketing and youth-involved intervention, where adolescents design and implement activities for their younger peers to promote healthy lifestyles.

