### 2.2. Study Design and Setting

The EYTO-kids project is a school-based pilot cluster randomized controlled intervention with a duration of 2 academic years (2015–2016 and 2016–2017) that is being conducted for 10 months in Reus, Spain. In Reus, 20 public primary schools and 8 high schools that serve low-income neighborhoods were identified. Of these schools, 4 public primary schools and 1 high school decided not to participate in this project. The randomization code was computer generated with Research Randomizer software (Geoffrey C. Urbaniak and Scott Plous, Lancaster, PA, USA) [20]. Furthermore, the unit responsible for the randomization was separate from the study researchers. Because the researchers knew the names of the schools, the allocation was not blinded. Then, the primary schools and high schools were assigned to the control or intervention arm at a ratio of 1:1 via an interactive electronic response system hosted by the Nutrition and Health Technology Centre (CTNS) in Reus, Spain. The unit responsible for the randomization will take no further part in the study. Because the researchers know the names of the 4 high schools, allocation concealment is not performed. The intervention group will receive the intervention; no intervention will be performed for the control group. An evaluation will be performed before and after the intervention in both participant groups (Figure 1). 

All participants will have informed consent forms signed by their parents or guardians. The EYTO-kids project has the approval of the Ethical Committee of the Hospital Universitari Sant Joan de Reus (ref: 16-01-28/1proj1), and the trial is registered with ClinicalTrials.gov (NCT02702336). The protocol is in accordance with the Helsinki Declaration and the Good Clinical Practice guidelines of the International Conference on Harmonization (ICH GCP). This randomized trial is being conducted according to CONSORT 2010 guidelines. Furthermore, this study adheres to the following Standard Protocol Items: Recommendations for Interventional Trials (SPIRIT) (Supplementary Materials 1) and Better reporting of interventions: template for intervention description and replication (TIDier) protocol guidelines (Supplementary Materials 2).

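### Section 2.6 states 90% power for a school-randomised trial with no allowance for clustering, so any positive school-level correlation puts power below the stated figure

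*Protocol article*

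**What the plan says.** Section 2.2 describes the design: "The EYTO-kids project is a school-based pilot cluster randomized controlled intervention". Allocation is 1:1 by school. The Abstract gives "eight primary schools and three high schools randomized into and designated the control group", with eight primary schools and four high schools in the intervention group. Outcomes are measured on the primary school children.

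Section 2.6 says the sample size is "calculated to detect a 5% rate difference among younger school peers who consume ≥1 fruit/day or practice ≥4 h/week of physical activity" between the two groups. It continues "For an alpha risk of 0.05 and a beta risk of 0.1 in a bilateral comparison" and gives 301 children in each group. It adds that a 30% loss is expected from experience in the previous EYTO study, without saying whether 301 is the number before or after that loss. The Abstract repeats 301 per group as a minimum.

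No ICC, design effect, cluster size or number of schools enters section 2.6, and no other section adjusts the number for clustering.

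**The concern.** Children in the same school share teachers, canteen, neighbourhood and, in the intervention arm, the same delivered sessions. Their answers on fruit intake and physical activity are likely to be correlated, so each child adds less information than an independent child would. A power statement that leaves this out in effect assumes an ICC of zero.

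What is at stake is how the result is read and reused. A null result would be taken as coming from a trial with 90% power for the stated difference, and a later full-scale trial could carry 301 per arm forward as an adequate number.

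**Working it through.** **Inputs from the article.** Two-sided alpha 0.05 and beta 0.1 (section 2.6); 301 children per arm (2.6 and Abstract); 30% loss (2.6); 8 primary schools per arm (Abstract).

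**Assumptions.** ICC of 0.01, 0.02 or 0.05, because the article gives none; equal school sizes; outcome compared once, after the intervention.

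**Step 1: can 301 be reproduced?** Not from the article, because no base rate is given. The usual two-proportion formula for a 5-point difference at 90% power and two-sided 0.05 needs, per arm and without clustering, 582 at a base rate of 5%, 918 at 10%, 1,464 at 20% and 2,053 at 40%. It returns about 301 only near a base rate of 1.2–1.3% or 93.7%. That is a separate problem and is set aside here by granting that the number gives exactly 90% under independence.

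**Step 2: could 301 already contain a design effect?** Between those two base rates the unclustered requirement exceeds 301, so there is no room for one. At a base rate of 0% the requirement is 203, so the largest factor 301 could hold is 301/203 = 1.48, before any loss.

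**Step 3: power under clustering.**

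- Children per school: m = 301/8 = 37.6, or 211/8 = 26.4 if 301 are enrolled and 0.7 × 301 = 211 are analysed.
- Design effect: DE = 1 + (m − 1) × ICC.
- Power, normal reference: Φ((1.960 + 1.2816)/√DE − 1.960).
- Power, small-sample reference: non-central t with 16 − 2 = 14 df and non-centrality 3.2415/√DE.

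Example at ICC 0.02, m = 37.6: DE = 1 + 36.6 × 0.02 = 1.73; 3.2415/√1.73 = 2.46; Φ(2.46 − 1.96) = Φ(0.50) = 0.69.

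| Analysed per arm (granted 90% under independence) | ICC | DE | Effective n per arm | Power, normal | Power, t on 14 df |
|---|---|---|---|---|---|
| 301 | 0.01 | 1.37 | 220 | 79% | 73% |
| 301 | 0.02 | 1.73 | 174 | 69% | 63% |
| 301 | 0.05 | 2.83 | 106 | 49% | 43% |
| 211 | 0.01 | 1.25 | 168 | 83% | 77% |
| 211 | 0.02 | 1.51 | 140 | 75% | 69% |
| 211 | 0.05 | 2.27 | 93 | 58% | 52% |

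The milder fall in the lower rows arises only because 211 has itself been granted 90%.

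**Step 4: would recruiting above the minimum restore 90%?** With 8 schools per arm fixed, an effective 301 needs n = 301 × (1 − ICC)/(1 − 301 × ICC/8). This is 478 per arm at ICC 0.01 and 1,192 at 0.02. At an ICC of 8/301 = 0.027 or more, no number of children is enough.

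**The case against.** **It is a labelled pilot and the article is condensed.** Both are true. But section 2.6 makes a formal 90% power claim for a between-group comparison and lists the inputs behind it. A fuller analysis plan could add detail; it could not make that number describe a cluster design.

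**The simple design effect may be too harsh.** Outcomes are measured before and after, and adjustment for baseline could reduce both the residual variance and the ICC. Also, 301 is a minimum, so actual numbers may be larger. Both points stand as reasons not to treat any single row of the table as the true power. Other features point the other way: unequal school sizes raise the design effect, and four high schools deliver the activities to the eight intervention primary schools, which may add correlation above the school level.

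**Stronger readings that the documents do not support.**

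- A reader might infer that 301 was derived by an individual-randomisation formula. The article shows only that no clustering allowance is stated. How 301 was obtained cannot be recovered.
- A reader might infer that the 16 schools, and not the 602 children, mainly set the information. The between-school share of the variance of a school mean is ICC/(ICC + (1 − ICC)/m). With m = 37.6 that is 28%, 43% and 66% at ICCs of 0.01, 0.02 and 0.05. Schools dominate only above about 1/(1 + 37.6) = 0.026.
- A reader might assume a 40% base rate and quote power of 18%, 15% and 11% for 5 points at these ICCs, or a detectable difference of about 15 to 22 points at 90% power. Without any clustering, 301 per arm at that base rate already gives only 24% power and a detectable difference of 13.1 points, so most of the power shortfall belongs to the base-rate question. The 40% is in no document, and the 15 to 22 points also rest on a normal reference and 301 analysed.

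**Conclusion.** The point holds: the article states a power that its own design does not have. On the most favourable footing for the sponsor, which accepts the 301 and uses a normal reference, power is about 79%, 69% and 49% at ICCs of 0.01, 0.02 and 0.05 with 301 analysed per arm, or about 83%, 75% and 58% with 211 analysed. The ICC values are assumptions; so are equal school sizes and a comparison without baseline adjustment. Once 301 (or 211) is granted 90% under independence, the direction needs only an ICC above zero.

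The conclusion is limited to the power statement. It does not show that the trial needs more schools, and it does not depend on any assumed base rate.

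**What to change.** Restate section 2.6 so that it:

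- gives the base rate for each primary outcome from the sponsor's own data;
- says whether 301 per arm is before or after the 30% loss;
- applies DE = 1 + (m − 1) × ICC with the resulting number of children per school, over a stated ICC range such as 0.01 to 0.05;
- uses a small-sample reference suited to 16 schools;
- reports the power or detectable difference that follows, and drops or qualifies the 90% claim.

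The detectable difference should come from the sponsor's base rate; the 15 to 22 point range at an assumed 40% should not be written into the plan. Reporting the estimated school ICC for each primary outcome would be a useful output of a pilot, but it is optional.

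The cost is rewording and a less favourable stated power. No schools or children are added.

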In early life, factors such as dietetic patterns, the balance of sedentary/active activities, poverty, housing, education and food security have been identified as the primary causes of the caloric imbalance and possible determinants of overweight status and obesity [35,36,37]. In Catalonia, 3 of 10 youths (2–17 years) present with excess weight [38]. Moreover, the most recent report from “*Enquesta de Salut General de Catalunya*” (2014) indicated that children under 15 years with a low socioeconomic status present with a higher overweight and obesity prevalence than children with a high socioeconomic status, with a 20.1% obesity prevalence and 16.1% overweight prevalence among the former group compared with 9.6% and 14.6%, respectively, among the latter group. Children under 14 years consume low amounts of fruit and vegetables, and only 8% of children under 14 years consume five portions of fruit and vegetables per day [38]. 

To include urban, low-income students, the EYTO-kids project is conducted in public primary schools and high schools. 

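### Section 2.6: 301 children per arm, a 5-point difference and 90% power are compatible only if the control rate is near 1% or 94%

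*Protocol article*

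**What the plan says.** Section 2.6 of the protocol article gives every input to the calculation except the control rate.

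- The target is "calculated to detect a 5% rate difference among younger school peers who consume ≥1 fruit/day or practice ≥4 h/week of physical activity", and the comparison is "between the intervention and control groups. For an alpha risk of 0.05".
- The error rates are stated: "For an alpha risk of 0.05 and a beta risk of 0.1 in a bilateral comparison".
- The result is that "301 primary schoolchildren are required in the first group (intervention), and 301 are required in the second group (control". The abstract repeats the figure as a minimum: "At least 301 younger school peers per group should be included".
- On attrition, section 2.6 adds: "An estimated 30% rate loss takes into account the losses observed in the previously conducted EYTO study". It does not say whether 301 is the number before or after this allowance.

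Both primary outcomes in section 2.5 are binary, and the aim is to "increase the percentage of younger school peers who consume ≥1 fruit/day and practice ≥4 h/week of physical activity". The article gives no control or baseline rate for either. The nearest figure is in the Discussion and concerns a different measure: "only 8% of children under 14 years consume five portions of fruit and vegetables per day".

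**The concern.** Detecting a 5-point difference between two independent proportions with 90% power usually takes many hundreds to a few thousand participants per arm. A figure of 301 is small enough to suggest that the difference, the power and the sample size do not belong together.

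This matters for reading the result. Someone who takes section 2.6 at face value would treat a null finding as good evidence against a 5-point effect. If the numbers give much less than 90% power for that effect, the inference fails. Section 2.6 is also the only justification the article offers for the sample size.

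**Working it through.** **Inputs.** From section 2.6: difference d = 0.05, two-sided alpha 0.05 (z = 1.96), power 0.90 (z = 1.2816), 301 per arm, 30% loss. The 5% is read as percentage points. A relative 5% would be a smaller difference at any rate and would need more children. The control rate p1 is not given and is varied below; p2 = p1 + 0.05. Clustering is ignored throughout.

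**Formula.** With m the mean of p1 and p2,

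n per arm = [1.96·√(2m(1−m)) + 1.2816·√(p1(1−p1) + p2(1−p2))]² / d²

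**Reproducing 301.** At p1 = 0.0125, p2 = 0.0625 and m = 0.0375, the two roots are 0.2687 and 0.2663. Then (1.96 × 0.2687 + 1.2816 × 0.2663)² / 0.0025 = 0.8679² / 0.0025 ≈ 301. The mirror case, 0.9375 against 0.9875, gives the same. Solving for n = 301 exactly gives p1 of about 1.2% or 93.8%.

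If 301 already includes the loss, 301 × 0.7 = 210.7, so about 211 are analysed. The solutions are then about 0.1% or 94.9%.

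**Other versions of the calculation, n = 301, control rates that reproduce it:**

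- unpooled variance: 1.2–1.4% or 93.6–93.8%
- continuity correction: 0.7–0.8% or 94.2–94.3%
- arcsine: 1.6–1.7% or 93.3–93.4%
- one-sided alpha: 2.0–2.2% or 92.8–93.0%
- 80% power: 2.4–2.7% or 92.3–92.6%

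None reaches a mid-range control rate.

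**A mid-range example.** At p1 = 0.30 and m = 0.325, the roots are 0.6624 and 0.6614, so n = (1.2983 + 0.8477)² / 0.0025 ≈ 1,842. Power with 301 is Φ[(0.05·√301 − 1.96 × 0.6624) / 0.6614] = Φ(−0.65) ≈ 26%.

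**Across assumed control rates:**

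| Control rate | n per arm for 90% power | Power, 301 analysed | Power, 211 analysed |
|---|---|---|---|
| 5% | 582 | 65% | 50% |
| 8% | 788 | 52% | 39% |
| 10% | 918 | 46% | 34% |
| 20% | 1,464 | 31% | 23% |
| 30% | 1,842 | 26% | 19% |
| 50% | 2,095 | 23% | 17.5% |
| 70% | 1,674 | 28% | 21% |
| 85% | 918 | 46% | 34% |
| 90% | 582 | 65% | 50% |

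The requirement peaks at about 2,100 near a rate of 47.5%.

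**Difference detectable with 90% power.** Solving the same formula for d at rates of 20% to 70% gives about 11 to 13 points with 301 analysed and 13 to 16 points with 211.

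**Precision.** The 95% interval for the difference has a half-width of at most 1.96·√(2 × 0.25/301) = 8.0 points with 301, or 1.96·√(2 × 0.25/211) = 9.5 points with 211.

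**The case against.** **An article may leave the control rate to the full protocol.** True, and its absence is not the fault alleged. The stated difference, power and number fail together at every rate from 8% to 85%, whatever the full protocol assumes within that range.

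**The rate could be extreme.** The documents do not exclude this outright. The 8% figure is for five portions of fruit and vegetables combined, so it is not a strict floor for one fruit a day. It says nothing against a rate near 94%, and nothing about physical activity. But the same 301 serves both primary outcomes, so both rates would have to be extreme. The trial aims to raise both, and the Discussion describes children's fruit and vegetable intake as low.

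**301 is a minimum.** The abstract does say so, and two whole grades in eight schools per arm might yield more. With an assumed 600 analysed per arm, power before clustering would be 81%, 55% and 42% at rates of 8%, 20% and 40%. This bears on the trial's eventual power, but does not make 301 the number required.

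**The analysis uses pre and post data.** Baseline adjustment helps: at an assumed pre-post correlation of 0.5, power with 301 rises from 46% to about 57% at a 10% rate, and from 31% to about 40% at 20%. Reaching 90% would take a correlation of about 0.82 to 0.93 at rates of 10% to 50%. Clustering by school pulls the other way, so the tabulated powers are neither an upper nor a lower bound.

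**It is a pilot.** A pilot need not have 90% power, but this one claims it.

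A reader might also infer that 301 came from a paired or one-sample calculation. The article shows no derivation, section 2.6 specifies a comparison between groups, and section 2.7 uses McNemar tests for change within each group. That origin is conjecture, and the point does not rely on it.

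**Conclusion.** Wrong as written. The combination in section 2.6 holds only at a control rate of about 1.2% or 93.8%, or about 0.1% or 94.9% if 211 are analysed. For assumed rates of 8% to 85%, 301 falls short of the number needed by a factor of about 2.6 (788/301) to 7 (2,099/301).

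A reader might go further and say that the trial's real power is 20% to 50%, or that it has almost no chance of finding a 5-point effect. The documents support neither. No control rate is given, power depends strongly on it, and with 301 analysed it is about 52% at a rate of 8% and 65% at 5% or 90%. The supported conclusion is that the stated 90% power does not follow from the stated inputs at ordinary control rates. The ranges above rest on assumed rates, independent children and a comparison of post-intervention proportions.

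**What to change.** In section 2.6:

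- Replace the claim of a 5% difference at 90% power with the difference the planned numbers can detect, or with the power for 5 points at a stated control rate for each primary outcome.
- Say whether 301 is the number enrolled (about 211 analysed) or the number analysed (301/0.7 = 430 to enrol).
- State the expected precision, and say that a null result will be read against it. The half-widths of about 8 points with 301 and 9.5 with 211 are before clustering, so the published figure should allow for it.

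Align the sentence in the abstract. The cost is the rewording of one paragraph and one abstract line. The stated power becomes less favourable, but no extra children are needed and the design is unchanged.
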